## 1. Background

The mortality and morbidity of Hepatocellular carcinoma (HCC) ranks first and third in refractory carcinoma, respectively. China is a high incidence country of HCC. The standard mortality rates of HCC of male adults and female adults were 14.52/100,000 and 5.61/100,000, respectively. That of HCC in such high incidence areas as QiDong, TongAn, ShunDe and etc. was over 30/100,000. Therefore, prevention and cure of HCC are severe in China.

With great accomplishment having been achieved, increase of early diagnosis of HCC and emergence of new treatment and technology for HCC, combined treatments for HCC based on surgery has been applied in clinical. However, difficulty in early diagnosis, low cure rates of the first operation, high recurrence rates and metastasis rates after a curative operation still exist without improvement. Especially recurrence of HCC after the curative operation is still an essential problem hindering improvements of surgeries for HCC.

### 1.1 Treatment for HCC after a surgery

Those include prevention and treatment for recurrence, in which the anti-recurrence treatment (adjuvant treatment after a surgery) including TACE, immunological treatment and immunoradiation treatment have been studied in recent years. Nevertheless, most of their effects have not been completely proved so far.

Effects of TACE have been proved in late stage of HCC, but without proof as an adjuvant method, mainly owing to inconsistency of conclusions of retrospective and prospective studies. In prospective studies, researchers found that TACE produced no effects with regard to anti-recurrence after the surgery even did harm. Lai etc. combined iodized oil, cis-platinum and epirubicin to treat HCC. Compared with the control group, there was no difference in the overall 3-year survival rates (66% vs. 65%) of the two groups. The 3-year tumor-free survival rate of treated patients was (18%) lower than that of patients in the control group (48%). However, most results of retrospective studies showed that TACE was effective in prevention of recurrences as an adjuvant method after the surgery. According to a retrospective study of 987 patients treated with TACE as an adjuvant method in Eastern Hepatobiliary Hospital, TACE prevented recurrence in some of patients with high recurrence. The recurrence rates of the study group and the control group were 22.2% and 61.1%, respectively.

Immunological treatment shows its potential value, but exact efficacy needs to be further tested and proved and its standards have not been established. Compared with other tumor, HCC has a clear relationship with infection of HBV, so theoretically, immunological treatment (thymic peptide and interferon) could improve immunity against tumor and hepatic virus, thus reducing recurrence rates. It was reported that tumor-free and overall survival rates of some of subtypes of HCC could be increased by interferon. Activity of hepatitis affected survival of the patients and antiviral treatment extended tumor-free survival after surgeries. However, those results have not been proved by large sample clinical trials.

Studies of radionuclide carriers with  $^{90}\text{Y}$ ,  $^{131}\text{I}$  and etc. in TACE initially proved their prevention of recurrence. Associated prospective randomized control trials with large samples are under progress.

### 1.2 Study of antitumor effect of $^{125}\text{I}$

Implantation of radionuclides within tissues for radiotherapy against carcinoma has been hundreds years. Radionuclides in early time were  $^{60}\text{Co}$ ,  $^{226}\text{Ra}$  and etc. with high energy  $\gamma$ -ray, a serious health hazard to patients and medical personnel who were hard to be protected, resulting in

restrictions of applications in clinical. In recent 20 years, such new low energy radionuclides as  $^{125}\text{I}$ ,  $^{103}\text{Pd}$  and etc. have widened indications of radiotherapy. Implantation of radionuclides within tissues could produce local radiation, as a result, target areas receive maximum doses of rays and doses in surrounding normal tissues dramatically decrease, which reduces side effects. In addition, target areas don't change with respiratory and body positions, so loss of volumes of tumor receiving radiotherapy significantly decrease. Recently,  $^{125}\text{I}$  has been applied in treatment of some carcinoma, such as pancreatic cancer, lung cancer, oral and maxillofacial cancer, head and neck cancer and etc. Radiotherapy is particularly effective in prostate cancer. With respect to liver foci there are some studies on implantation of  $^{125}\text{I}$  to treat liver metastasis of colon cancer but no studies on  $^{125}\text{I}$  for anti-recurrence after surgeries for HCC.

In order to assess the efficacy of implantation of  $^{125}\text{I}$  as an adjuvant method to treat HCC indicating surgeries before, a randomized control trial was run to see whether  $^{125}\text{I}$  could prevent recurrence after curative surgery of HCC, improve prognosis and reveal its side effects at the same time.

## **2. Objectives**

- (1) To assess the efficacy and safety of prevention of recurrence of  $^{125}\text{I}$  after surgeries for HCC.
- (2) To develop a rational, effective and standardized adjuvant treatment protocol of prevention of recurrence with  $^{125}\text{I}$  after surgeries of HCC.

## **3. Flow diagram**

[figure not shown]

#### 4. Introduction of the study

##### 4.1 Study Design

It is a prospective randomized clinical control trial, assessing the efficacy and safety of prevention of recurrence of  $^{125}\text{I}$  after surgeries for HCC, from which a rational, effective and standardized adjuvant treatment protocol of prevention of recurrence with  $^{125}\text{I}$  after surgeries of HCC could be developed.

## 4.2 Population and Period

The total number of cases is 68.

It was reported that the median tumor-free survival time or median recurrence time was 13-24 months after a curative surgery for HCC. In this study, the median recurrence time of the control group is supposed to be 18 months. That of the group of patients with implantation of  $^{125}\text{I}$  is expected to be 36 months (the hazard ratio of  $^{125}\text{I}$  was 0.5). A probability value of  $<0.05$  in one-sided test is considered statistically significant. Power of the test was 0.80. The number of cases in the study is 68.

These patients will be treated in our hospital from July 2000 to June 2004. The follow-up period was extended to 5 years after surgery.

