#### **13.2 Statistical analysis**

Professional statistical workers will undertake statistical analysis tasks, and participated in the whole process from experimental design and implementation to analysis and summarization. After the completion of the trial protocol and CRF, the development of statistical analysis plan is formulated, and the statistical analysis report will be provided after the necessary changes in the analysis during the testing process.

Statistical methods: the statistical quantitative index include mean, standard deviation, median, minimum, maximum. All statistical tests use two-sided test,  $P \leq 0.05$  is considered to have statistically significant difference. The comparison among enumeration data use  $\chi^2$  test. The inter-group comparison of measurement data took use of t test after normal step test and homogeneity test for variance. We use life table for the estimation of survival rate, Log-rank test for the comparison of survival rate among groups and Kaplan-Meier method for survival curves. COX regression analysis will be for the relevant factors affecting patients' survival.

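### Sections 4.2 and 13.2 set different success rules for time to recurrence: the 68 patients give 80% power only under the one-sided rule, and about 72% under the two-sided one

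*Protocol*

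**What the plan says.** **Section 4.2 (Population and Period).** "The total number of cases is 68". The planning assumptions are that "the median recurrence time of the control group is supposed to be 18 months" and that the median in the implanted group "is expected to be 36 months (the hazard ratio of" the implant is given as 0.5). A probability below 0.05 "in one-sided test is considered statistically significant. Power of the test was 0.80. The number of cases in the study is 68". Patients are treated from July 2000 to June 2004, with follow-up to 5 years after surgery.

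**Section 13.2 (Statistical analysis).** "All statistical tests use two-sided test", with P at or below 0.05 counted as significant. The section names the "Log-rank test for the comparison of survival rate among groups".

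**Section 10.1** makes time to recurrence (TTR) the main endpoint. **Section 4.4** says that allocation is random but gives no ratio.

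**The concern.** Section 4.2 does more than record a planning input: it says what counts as significant, and it says so for a one-sided test. Section 13.2 says what counts as significant for every test, and it says two-sided. Each applies to TTR, and they differ.

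Two things are at stake.

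- **The power statement.** If section 13.2 governs the primary test, the 80% in section 4.2 describes a test that will not be used.
- **The decision rule.** A result in favour of the implant with a two-sided p-value between 0.05 and 0.10 (one-sided 0.025 to 0.05) succeeds under section 4.2 and fails under section 13.2. Section 13.2 also has the analysis plan written after the protocol and allows for changes to the analysis while the trial runs. The choice could therefore be made late.

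**Working it through.** **Inputs.** From section 4.2: N = 68, medians 18 and 36 months, hazard ratio 0.5, alpha 0.05, power 0.80, follow-up 60 months after surgery. Assumed because the protocol does not state them: 1:1 allocation (34 per arm), exponential times, and no loss to follow-up. Normal quantiles: 1.645 (one-sided 5%), 1.960 (two-sided 5%), 0.842 (80% power). (ln 0.5)² = 0.4805.

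**Step 1: expected recurrences in 68 patients.**
- Control: 1 − 2^(−60/18) = 0.901
- Implant: 1 − 2^(−60/36) = 0.685
- Mean 0.793; 68 × 0.793 = 53.9 events

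**Step 2: reproduce the plan's figure under the one-sided rule.**
- Schoenfeld events: 4 × (1.645 + 0.842)² / 0.4805 = 51.5, so 52.
- Patients: 52 / 0.793 = 65.6, so 66.
- With the variance of the log hazard ratio taken as 1/d₁ + 1/d₂, patients per arm are (1.645 + 0.842)² × (1/0.901 + 1/0.685) / 0.4805 = 33.1, so 34 per arm and **68 in total**.
- Schoenfeld power with 53.9 events: Φ(√(53.9/4) × 0.693 − 1.645) = Φ(2.545 − 1.645) = **0.816**.

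The stated 68 and 80% are therefore sound for a one-sided 5% test.

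**Step 3: the same design under the two-sided rule.**
- Events for 80% power: 4 × (1.960 + 0.842)² / 0.4805 = 65.3, so 66.
- Patients: 66 / 0.793 = 83.2, so 84. The two-sided rule does not give 68.
- Power with 53.9 events: Φ(2.545 − 1.960) = **0.721**.
- A log-rank simulation of 20,000 trials gave 0.817 one-sided and 0.721 two-sided.

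**Step 4: how far the two-sided figure moves.**

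| Reading | Events | Two-sided power |
|---|---|---|
| Schoenfeld, 60 months each | 53.9 | 72.1% |
| Variance 1/d₁ + 1/d₂, 60 months each | 53.9 | 71.3% |
| Freedman, 60 months each | 53.9 | 68.7% |
| Schoenfeld, all followed to 5 years after the last surgery (uniform accrual over 48 months) | 59.5 | 76.2% |
| Schoenfeld, 60 months, assumed 5% yearly loss | 49.3 | 68.2% |

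A design with exactly 80% one-sided power has two-sided power Φ(1.645 + 0.842 − 1.960) = 70.1%.

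**Step 5: the effect detectable with 80% two-sided power.** With 53.9 events held fixed, the hazard ratio is exp(−2.802 / √(53.9/4)) = 0.466. A smaller hazard ratio also means fewer recurrences in the implant arm. At 0.463 the expected count is 53.0 and power is 80.0%; at 0.47 it is 53.1 and 78.6%. The self-consistent value is therefore about 0.46.

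**Step 6: how often the two rules would disagree.** Under the planned effect, 0.816 − 0.721 = 0.095, so about one trial in ten would be positive under section 4.2 and not under section 13.2.

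**The case against.** The strongest reply is that section 4.2 contains no miscalculation. For the test that it names, 68 patients do give about 80% power. The protocol also never says that section 13.2 takes precedence. A reader might infer that the sample size was computed wrongly, or that the trial simply has 72% power and is too small. The documents do not support either: the 72% is conditional on the two-sided rule governing TTR. That limit stands. It does not remove the contradiction, because section 13.2 covers all tests and makes no exception.

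A second reply is that 72% looks more exact than it is. This is fair. Allocation ratio, loss to follow-up and the distribution of times are not stated. Section 10.1 ends TTR at loss or unexplained death without saying whether that point is an event or a censoring, so the event count is itself uncertain. The figure should carry its assumptions and a range. None of the readings checked in step 4 reaches 80%.

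A third concerns error rates. A reader might infer that the false-positive rate for benefit exceeds what the protocol allows. It does not. Using the one-sided rule raises that rate from 2.5% to 5%, but 5% is the level that section 4.2 openly names. The problem is that the level is not fixed in advance.

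Finally, a later analysis plan might choose one rule. It would then have to depart from one of the two protocol sections, and if it chose the two-sided rule the 80% would still be wrong.

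**Conclusion.** The contradiction is real and bears on the primary success criterion. Section 4.2's figures hold under its own one-sided rule. Under section 13.2's two-sided rule, power at a hazard ratio of 0.5 is about 72%, so the risk of missing the planned effect is about 28% against the stated 20%.

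The 72% rests on 1:1 allocation, exponential times, 60 months of follow-up for each patient and no loss. The range is roughly 69% to 76% by formula and follow-up reading, and about 68% with an assumed 5% yearly loss. The direction does not depend on these choices.

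It does not follow that the trial must enrol more patients. What must be corrected is the rule and the statement of power that goes with it.

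**What to change.** State one rule for TTR in both sections before the analysis.

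**Preferred.** Keep the two-sided 0.05 log-rank test of section 13.2 as the rule for TTR, delete the one-sided statement in section 4.2, and put in its place:

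> With 68 patients (1:1) followed for 5 years without loss (about 54 recurrences), the two-sided 5% log-rank test has about 72% power for a hazard ratio of 0.5; 80% power is reached at a hazard ratio of about 0.46.

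**Alternative.** If the sponsor intends a one-sided primary test, section 13.2 must say so explicitly for TTR and justify it. The 80% in section 4.2 can then stay.

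**Cost.** Wording only. The preferred route needs no extra patients; its price is a less favourable stated power.

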## 4.3 Grouping

All of the patients will be grouped after receiving curative surgeries for HCC.

$^{125}\text{I}$  treated group: The wound will carefully stanch after the tumor have been removed completely. The square meter of the wound will be measured and the data will be input into the computer to determine the number of radionuclides will implant and doses. Mick radionuclide applicator will be used to implant  $^{125}\text{I}$  at 1cm interval in the normal liver tissues at the incisional margin ( $^{125}\text{I}$  was produced in Reactor Engineering Research of China Institute of Atomic Energy with  $0.8\text{mm} \times 4.5\text{mm}$  and a half-life of 59.6 days and enveloped with Nickel titanium alloy. It is sterilized under high temperature. It has X-ray with energy of 27.4-31.5Kev and  $\gamma$ -ray with energy of 35.5 Kev. The activity of per seed is 0.5-0.6mCi). Ultrasonography is utilized to see whether seeds are well-distributed. More seeds will be implanted so as to avoid cold spot areas if seeds are not well-distributed. Fibrin gel will be smeared on wounds and then sutured with absorbable gelatin sponge or hemostatic gauze to prevent  $^{125}\text{I}$  from dropping off.

Control group: The rest treatment will be the same as that of the  $^{125}\text{I}$  treated group except for implantation of  $^{125}\text{I}$ .

Both of the groups received identical routine support treatment for the liver after surgery.

All of the patients will receive venous blood collection on one day before surgeries and day 7 after surgery. Aminotransferase and bilirubin were measured. AFP and MMP-9 will be measured via radioimmunoassay. Meanwhile, activity of nature killer cells and T cell subsets will be measured by flow cytometers (America COULTER). Curative hepatectomy of HCC must meet these following conditions: a. Tumor is completely removed. Explorations during surgery show no tumor remaining and fast pathology results revealed that there are no cancer cells in the incisional margins. b. There are no macroscopic cancer emboli in the main side branches and bile duct bifurcations. c. The number of the tumor is less than three. d. There is no extrahepatic metastasis.

## 4.4 Randomization

Patients included in the study will be allocated randomly. Random digits will be generated by computer. Custody of the random number table by hand.

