## 4.5 Patients

### 4.5.1 Inclusion criteria

(1) Volunteer patients with good compliance and ranging from 18 to 70 years.

(2) Patients meeting these following conditions:

- Tumor has been removed completely via evaluations.
- The pathological diagnosis is HCC.
- The maximum diameter of a single tumor is less than or equal to 10cm and greater than or

equal to 2cm.

- The number of the tumor is less than three and the maximum diameter is less than or equal to 5cm regarding multiple nodule.
- No macroscopic vessel invasion.

(3) Other functions of organs are normal.

(4) KPS is over 70.

(5) Child-pugh stage A.

(6) The latest results of laboratory tests should meet these following standards:

- $HgB \geq 9.0g/dl$ .
- The count of neutrophils is more than 1,500/mm.
- The count of platelets is more than 50,000/ul.
- The levels of ALT and AST are lower than or equal to twice normal ceiling values.
- The level of serum creatinine is less than or equal to 1.5 times normal ceiling values.

(7) The HCG test of women with fertility should be negative within 14 days before treatment.

(8) Patients who meet all the above conditions sign written informed consents.

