7.2.2 The procedure of preservation and distribution

Each patient of the group will obtain a random number, and then the number will be reported to the preservers of the center by the researchers. The preservers would judge whether to use seeds which will be distributed to the patients with the corresponding number.

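### Allocation is specified only as computer random digits and the TTR log-rank ignores tumour burden: valid, but it gives up a few points of power that one stratification factor would recover

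*Protocol*

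**What the plan says.** Protocol section 4.4 states that patients are allocated at random and adds "Random digits will be generated by computer" and "Custody of the random number table by hand". Section 7.2.2 describes how the list is used: "Each patient of the group will obtain a random number", which is reported to the custodian of the seeds, who decides whether seeds are issued. No stratum is reported with it. Allocation ratio, blocks and strata appear nowhere in the protocol.

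Section 4.2 fixes the size and the period: "The total number of cases is 68" and "These patients will be treated in our hospital from July 2000 to June 2004".

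Section 4.5.1 admits single tumours from 2 to 10 cm and, for multiple tumours, "The number of the tumor is less than three and the maximum diameter is less than or equal to 5cm regarding multiple nodule". 

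Section 13.2 compares survival between groups by a log-rank test with no strata. It plans Cox regression for factors related to survival, but names no covariates and does not tie the model to the comparison of time to recurrence (TTR), the main endpoint in section 10.1.

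**The concern.** Sixty-eight patients over four years is a small trial in which to leave a strong prognostic factor both unbalanced and unadjusted. Tumour burden is the obvious candidate, given the range admitted. Two things follow if it is prognostic. First, its share can differ between arms by chance and move the observed hazard ratio. Second, even with perfect balance, a log-rank test that ignores it works on a hazard ratio diluted towards 1. Both reduce the chance of detecting the planned effect, and a visible imbalance in a small open surgical trial invites argument about the result. At stake is precision, not validity.

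**Working it through.** **Inputs.** From section 4.2: N = 68; "the median recurrence time of the control group is supposed to be 18 months"; 36 months with seeds (HR 0.5); one-sided 0.05; power 0.80; "The follow-up period was extended to 5 years after surgery" (60 months per patient). Assumed, because the protocol gives no figure: 1:1 allocation, prevalence p of high tumour burden, and its prognostic hazard ratio h.

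**The plan's own figure.** Schoenfeld events = 4 × (1.645 + 0.842)² / (ln 0.5)² = 4 × 6.18 / 0.480 = 51.5, so 52. Mean event probability over 60 months = 1 − (e^(−60 ln2/18) + e^(−60 ln2/36))/2 = 1 − (0.099 + 0.315)/2 = 0.793. N = 52/0.793 = 66, within 2 of the stated 68. With 68 patients, about 54 events are expected. The SE of log HR is 2/√54 = 0.272, and power is 81.6% if no prognostic factor is at work.

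**Step 1: power under the plan and under the alternative.** Simulated trials with control median 18 months, HR 0.5, 60-month follow-up, one-sided 0.05 and p = 0.45:

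| Prognostic HR | Simple list, plain log-rank | Stratified blocks, stratified log-rank |
|---|---|---|
| 1 | 82% | 81% |
| 1.5 | 79% | 81% |
| 2 | 75% | 79% |
| 3 | 68% | 78% |

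**Step 2: where the gain comes from.** A separate run of 20,000 trials per setting at h = 2 gave:

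- simple list, plain test: 75.3%
- stratified list, plain test: 76.8%
- simple list, stratified test: 78.8%
- both stratified: 80.0%

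The stratified test alone therefore brings 3.5 of the 4.7 points. Dilution explains this: at p = 0.5 with exact balance, the unadjusted Cox hazard ratio is 0.509, 0.524 or 0.556 for h = 1.5, 2 or 3, against a true 0.50.

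**Step 3: chance that imbalance shifts the HR by 15% or more, in either direction.** On a simple list the between-arm difference in share has SD = √(4p(1−p)/68), and the shift in log HR is about difference × ln h. For p = 0.5 and h = 2, SD = 0.121; the difference needed is ln 1.15 / ln 2 = 0.140/0.693 = 0.202; z = 1.66; probability 9.6%. Across the assumptions:

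| h | p = 0.2 | p = 0.3 | p = 0.5 |
|---|---|---|---|
| 1.5 | 0.04% | 0.19% | 0.45% |
| 2 | 3.8% | 7.0% | 9.6% |
| 2.5 | 11.6% | 17.0% | 20.9% |
| 3 | 19.0% | 25.2% | 29.4% |

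Allowing for the dilution in the Cox model, p = 0.5 and h = 2 needs a difference of 0.212, and the probability falls to 8.0%. A shift of 15% is 0.140/0.272 = 0.51 standard errors. The chance of a shift in one given direction is about half the figure shown.

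**Step 4: which restriction removes it.** In 100,000 simulated lists at p = 0.5 and h = 2, a shift of this size occurred in 10.5% with a simple list, 11.4% with blocks of 4 and no strata, and none with blocks of 4 within two strata. The SD of the share difference was 0.122, 0.121 and 0.019. Stratification does the work on tumour burden.

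**Step 5: what blocks add.** On a simple list of 68 the arm sizes differ by 12 or more with probability 18%, but this costs little: at 26:42 (that split or worse has probability 6.8%) power is 79.7% against 81.6%. The first 34 patients split 12:22 or worse with probability 12%, which short blocks prevent.

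**The case against.** The strongest reply is that simple randomisation is a sound method and chance imbalance is not an error. It is symmetric, and the standard error of the log-rank test already allows for it. That stands. Even at p = 0.5 and h = 2, the factor adds an SD of 0.121 × 0.693 = 0.084 to the log HR against an SE of 0.272, which is under 10% of the variance.

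Second, a reader might infer that the list is known to be unrestricted. The documents do not support that: computer-generated digits and a numbered list held by a custodian fit a blocked or stratified list too. What can be said is that the protocol states no restriction and so permits none. The list must exist before the first patient is allocated, so it is reasonable to settle this in the protocol.

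Third, a reader might quote a 10% chance of a 15% shift as a property of this trial. It is not. It needs a factor present in about half the patients that doubles the recurrence hazard, and the protocol gives neither figure. Other criteria also narrow the risk: Child-Pugh A, no macroscopic vessel invasion, clear margins and no prior treatment.

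Fourth, the choice of stratum is a judgement, imaging before surgery may differ from the operative findings, and small blocks in an open single-hospital trial make allocation easier to guess. All true. They limit the gain or carry a modest cost, but do not remove the benefit of a stratified test.

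**Conclusion.** The point holds as one of efficiency. The plan is valid, and nothing here shows bias or type I error inflation. It leaves about 2, 4 or 10 points of power unused at a prognostic HR of 1.5, 2 or 3 with an assumed 45% prevalence, and risks at most about 1 point if tumour burden turns out not to be prognostic. Most of the gain at a prognostic HR of 2 comes from the stratified test. Stratified allocation removes the chance imbalance in the factor, whose probability of moving the HR by 15% or more ranges from about 0.04% to 29% over prevalence 0.2–0.5 and prognostic HR 1.5–3. Blocks alone would not reduce that probability; they mainly control arm sizes and balance over calendar time. All power figures use the one-sided basis of section 4.2 and assume 1:1 allocation.

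**What to change.** In section 4.4, state 1:1 allocation by a computer-generated list in random permuted blocks whose sizes are not disclosed to the surgeons, stratified by one two-level pre-operative tumour-burden factor. An example is a single tumour up to 5 cm versus a larger single tumour or two nodules; the cut is for the sponsor to choose. The imaging needed is already required by section 8.1. In section 7.2.2, have the stratum settled and reported with the patient before the number is given. In section 13.2, make the primary TTR log-rank stratified by the same factor, using the stratum recorded at allocation.

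The cost is a new list, a few sentences and slightly more predictable allocation in an open single-hospital trial, limited by varying the block sizes and keeping to one factor. If the sponsor does not accept that, keep the simple list, state the ratio and method openly, and adopt the stratified TTR log-rank alone.
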